### Control group

Participants assigned to the control group receive usual care at the Department of Oncology. They will undergo all study measurements at the defined timepoints, similar to the intervention group. For ethical reasons, the participants are informed of the possibility of being referred to training and rehabilitation at municipal service providers through the Department of Oncology. The participants will receive advice regarding training from the physiotherapist during baseline assessments.

### Study timeline

Recruitment of participants started in late February 2024. The project is scheduled to conclude at the latest in June 2025. The 24-week study period includes four assessment time points: baseline (T1), midpoint of the exercise program after 6 weeks (T2), completion of the exercise program at 12 weeks (T3), and a 12-week follow-up after the intervention period (T4).

### Baseline data

After obtaining written consent, baseline data are collected. Information regarding age, ECOG performance status, current medications, location of metastases, and contact information are registered in REDCap [42]. Furthermore, the participants are mailed an electronic baseline questionnaire including questions on demographic information (living arrangements, educational level, and employment status), health information (comorbidities and current medications), and lifestyle factors (current physical activity level, barriers to and facilitators of exercise, diet, and alcohol consumption). The questionnaire is based on the baseline questionnaire used in the Body & Cancer Program [53] and a dietary questionnaire used at Steno Diabetes Center Aarhus.

### Feasibility outcomes

Multiple feasibility outcomes are investigated in this study:Recruitment rate, consisting of the proportion of eligible participants who choose to participate in the study.Adherence to the exercise program, measured as the attendance rate.Retention, defined as the percentage of consenting participants in the intervention and control group completing T3.Acceptability, defined as the participants’ satisfaction with the study and intervention, employing both quantitative (ad hoc questions using Likert-scale scoring and open-ended questions) and qualitative (semi-structured interviews) methods.Adherence to other study procedures, i.e., the rate of completed questionnaires and collected biomarker samples.

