One potential avenue to combat these adverse outcomes in patients with MBC is through exercise. In recent international guidelines, exercise is recommended in the curative setting alongside and after conventional treatments to reduce side effects and improve survival [28, 29]. However, no recommendations are provided in the metastatic setting, as evidence of the beneficial effects of exercise in these patients is scarce. While multiple prospective studies have investigated exercise interventions in the curative BC setting, patients with MBC are often not included, even though exercise is found to be safe [30], including for those with bone metastases [31].

A few studies have investigated the effects of exercise in the MBC setting with inconsistent results. In the PREFERABLE-EFFECT study by Hiensch et al. [32], 357 patients were randomized to a 9-month supervised exercise program versus usual care. While exercise was found to significantly improve HRQoL and fatigue, the authors did not examine outcomes on body composition and metabolic health. Scott et al. [33] randomized 65 patients with MBC in treatment with chemotherapy to a 12-week aerobic training program versus a stretching control group. Aerobic training was found to be safe, however not feasible, as almost one-third (N = 9/33) in the intervention group discontinued due to disease progression, lack of motivation or pain.

In a pilot trial, Sheean et al. [34] investigated a 12-week exercise and nutritional intervention versus a wait-list control condition in patients with MBC (*N* = 40), providing lifestyle coaching and intervention support for home-based training. The intervention was deemed feasible and safe and resulted in improvements in HRQoL, fatigue, endocrine symptoms, and visceral fat mass. Results from a full-scale study have yet to be published.

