### Randomization

Recruited participants undergo non-stratified, simple randomization in a 2:1 ratio to either intervention or usual care. The randomization sequence is computer-generated independently through an algorithm used by the Clinical Trial Unit at Aarhus University. When the participants have been randomized, their allocation will be locked in the Research Electronic Data Capture (REDCap) software [42, 43]. The randomization process is not blinded for researchers or participants, as it is not compatible with the study design. Randomization allocation is delivered orally to participants.

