### Sample size

As this study is a feasibility trial, no formal sample size calculation was performed, which aligns with published recommendations [40, 41, 44]. The chosen sample size of 21 participants was based on practical considerations, including recruitment potential, funding constraints, and the high level of participant engagement required for an exercise intervention in this patient population. This decision was also informed by previous feasibility studies investigating exercise interventions in cancer populations with similar feasibility outcomes [45–48]. Recommendations for pilot trials typically suggest a sample size of 10 to 40 participants per group [49–51]. Our 2:1 randomization design (14 interventions, 7 controls) does not fully align with these recommendations due to practical constraints and the need to prioritize intervention feasibility while still maintaining a control group for study design experience and exploratory comparisons. However, the total sample size of 21 participants is consistent with feasibility study guidelines, which emphasize that smaller sample sizes are appropriate when assessing process-related outcomes rather than effect sizes [44].

In the interest of transparency, we acknowledge the precision limitations of our feasibility estimates. Assuming an 80% retention rate with *N* = 21, the 95% confidence interval ranges from 62 to 98%. This wide interval is an inherent limitation of feasibility studies but does not invalidate the study’s objectives. While retention rates in pilot trials are often used to inform sample size calculations for definitive trials, this is not the objective of our study. Instead, our focus is on determining whether trial procedures are practical and achievable within study context.

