### Progression criteria

To ensure that the feasibility objectives in this study are met, progression criteria for each objective are developed [74]. Defining progression criteria is necessary in the interpretation of trial findings. For this purpose, a traffic light system is employed. In this system, a lower (red) threshold indicates major problems that require urgent attention (and perhaps are unfixable), amber indicates minor problems that require attention, and green indicates areas of no concern [74]. As estimates of rates in the feasibility measures are subject to uncertainty, this system allows for chance variation in contrast to definitive thresholds. We will identify fundamental feasibility measures to accurately weigh the importance of each outcome in the assessment. In Table 1, the progression criteria for each outcome are outlined. These criteria are based on relevant studies, as referenced in the background section, and informed by prior research on feasibility outcomes in exercise interventions for breast cancer populations. To provide an overall assessment of the feasibility of the study, we employ a holistic approach, using quantitative measurements of the progression criteria, data from the evaluation questionnaire, and data on feasibility from the qualitative interviews collectively.

**Table 1 Tab1:** Progression criteria for feasibility objectives

Feasibility objective	Red Major problem	Amber Minor problem	Green No concern	Fundamental objective
Recruitment rate	< 25%	25–33%	≥ 33%	Yes
Attendance rate	< 70%	70–80%	≥ 80%	Yes
Retention rate	< 65%	65–80%	≥ 80%	Yes
Acceptability of intervention^a^	< 75%	75–90%	≥ 90%	Yes
Adherence to other study procedures	< 80%	80–90%	≥ 90%	No

Lower and upper threshold values in the traffic light system for feasibility outcomes

^a^Percentage of participants in the intervention group that answers “Yes” to the question: “Would you recommend others to participate in the physical activity program?” in the evaluation questionnaire

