## Discussion

Patients with MBC often experience a decrease in HRQoL and reduced physical functioning, and patients with ER + disease receiving endocrine-based treatment also have an increased risk of weight gain and adverse metabolic effects. To reduce cancer- and treatment-related side effects, exercise is recommended for BC patients in the curative and adjuvant settings. In contrast, evidence in the metastatic setting remains limited, and no study has yet investigated exercise in endocrine-treated patients with MBC and overweight. The overall purpose of the present study is to develop a feasible exercise intervention to support improved metabolic health, body composition, and patient-reported outcomes for MBC patients in endocrine therapy with overweight.

The intervention design is based on evidence from the curative and adjuvant BC settings. Exercise programs lasting 12 weeks or longer are reported to have positive effects by using combined aerobic and resistance training [80]. Furthermore, our intervention is designed to be intense, but at the same time not too time-consuming, deciding on three weekly training sessions for 12 weeks. The training sessions are planned to take place in the afternoon on weekdays to accommodate patients with MBC who still work [81].

We opted for an unequal randomization ratio (2:1) to enhance the assessment of feasibility objectives, such as adherence, retention, and acceptability, which are directly tied to the intervention. This design provides greater precision in evaluating these outcomes compared to a 1:1 ratio. Additionally, the unequal allocation addresses ethical considerations by minimizing the number of participants assigned to the control group, ensuring more participants benefit from the intervention. The control group remains essential for collecting data on comparator group design, bias reduction, and addressing ethical dilemmas for a future trial.

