### Strengths and limitations

A methodological strength of the present feasibility study is that we follow good practice recommendations for pilot and feasibility studies [82] as well as the SPIRIT checklist for reporting the study protocol. Another strength is that we employ both self-reported and objective data measurements to estimate effects, and we use quantitative and qualitative approaches to evaluate feasibility.

In the study design, we employ a randomized controlled study design, which is important for testing the feasibility of the overall study methodology and intervention. However, as the control group is small, with seven participants, the purpose hereof is to test the feasibility of including a usual care control group rather than conducting hypothesis testing. Another strength in the study design is the long period of follow-up and the use of multiple measurement points. Furthermore, we take precautionary measures to prevent missing data, such as sending reminder emails and providing physical reminders to participants. A strength of our exercise intervention is that it is delivered in person by highly skilled personnel experienced in working with cancer patients.

Some limitations should also be noted. First, with a sample size of 21 participants, the study is rather small and not powered for hypothesis testing. However, as a feasibility trial, the primary aim is not to detect statistical differences but to assess the practicality of conducting a larger trial. The chosen sample size was based on pragmatic considerations, including recruitment feasibility within the given timeframe, resource availability, and the high level of participant engagement required for an exercise intervention. While we recognize that the precision of feasibility estimates is inherently limited in small feasibility studies, our approach incorporates both quantitative and qualitative data that we are confident will provide a comprehensive evaluation.

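### Retention is graded as one rate over both arms, so it can be green with a red control arm or an amber exercise arm, and it does not match the precision argument for 2:1 allocation

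*Protocol article*

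**What the plan says.** All references are to the protocol article.

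- **Feasibility outcomes** gives one definition: "Retention, defined as the percentage of consenting participants in the intervention and control group completing T3". T3 is the 12-week assessment.
- **Progression criteria, Table 1** has one retention row: red below 65%, amber 65–80%, green from 80%. It is marked as a fundamental objective and is not split by arm. The acceptability row, by contrast, carries a footnote limiting it to the intervention group.
- **Sample size** plans 14 intervention and 7 control participants. For 80% retention with N = 21 it says "the 95% confidence interval ranges from 62 to 98" percent.
- **Randomization** states: "Recruited participants undergo non-stratified, simple randomization in a 2:1 ratio to either intervention or usual care". The 14/7 split is thus an expectation, not a guarantee.
- **Discussion** counts retention among the outcomes bound up with the intervention and says of the 2:1 ratio: "This design provides greater precision in evaluating these outcomes compared to a 1:1 ratio".
- **Strengths and limitations** says of the seven-person control arm that "the purpose hereof is to test the feasibility of including a usual care control group".
- **Progression criteria** and **Discussion** add that overall feasibility is judged holistically, from the criteria, questionnaires and interviews together, and that a steering committee decides whether to proceed.

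**The concern.** Retention answers a different question in each arm. In the exercise arm it shows whether patients stay through a programme of three sessions a week. In the control arm it shows whether patients stay after being allocated to usual care. One combined percentage lets good retention in one arm offset poor retention in the other.

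Two things are at stake. First, green means no concern on a fundamental objective, and that colour informs the decision on the definitive trial. Marked differential drop-out, which would threaten a full-scale comparison with bias, could sit under a green light. Second, the protocol is at odds with itself: it justifies 2:1 allocation partly by better precision for retention, but the retention rate that it grades uses everyone, whatever the ratio.

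**Working it through.** **1. The plan's own interval.** With p = 0.80 and n = 21, the standard error is √(0.80 × 0.20 / 21) = 0.0873. The t quantile on 20 df is 2.086, so the interval is 0.80 ± 2.086 × 0.0873 = 0.80 ± 0.182, or 61.8% to 98.2%. This rounds to the stated 62–98%. The normal quantile gives 62.9–97.1%. The arithmetic is sound, and the denominator is all 21 participants.

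**2. Thresholds as counts at 14/7**

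| | Green (≥ 80%) | Amber | Red (< 65%) |
|---|---|---|---|
| Pooled, 21 | ≥ 17 (81.0%) | 14–16 (66.7–76.2%) | ≤ 13 (61.9%) |
| Exercise, 14 | ≥ 12 (85.7%) | 10–11 (71.4–78.6%) | ≤ 9 (64.3%) |
| Control, 7 | ≥ 6 (85.7%) | 5 (71.4%) | ≤ 4 (57.1%) |

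**3. What a pooled green can contain.** Green allows 21 − 17 = 4 losses.

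- All four in controls: 14/14 + 3/7 = 17/21 = 81.0%. Pooled green, control 42.9%, red.
- Three in controls, one in exercise: 13/14 + 4/7 = 17/21. Pooled green, control 57.1%, red.
- All four in exercise: 10/14 + 7/7 = 17/21. Pooled green, exercise 71.4%, amber.
- Five in exercise: 9/14 + 7/7 = 16/21 = 76.2%. Exercise red, but pooled amber. At 14/7 a red exercise arm never scores green.

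**4. Other splits.** Under simple 2:1 randomization the exercise arm has size M ~ Binomial(21, 2/3). A red exercise arm with pooled green needs M ≤ 11, for example 7/11 (63.6%) + 10/10 = 17/21. P(M ≤ 11) = 0.125. That is the chance of such a split, not of the event itself.

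**5. How often, under assumed true retention rates.** These rates are illustrative and not from the protocol. The calculation sums Binomial(14, p₁) × Binomial(7, p₂) over all outcomes with at least 17 completers.

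| Exercise p₁ | Control p₂ | P(pooled green) | Of which |
|---|---|---|---|
| 0.95 | 0.50 | 0.59 | control red: 0.365 |
| 0.90 | 0.50 | 0.42 | control red: 0.22 |
| 0.70 | 0.95 | 0.51 | exercise below green: 0.35 |
| 0.70 | 0.90 | 0.43 | exercise below green: 0.27 |

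For comparison, at p₁ = 0.70 the exercise arm on its own is green (≥ 12/14) with probability 0.16.

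**6. The precision claim.** At 80% retention the standard error is √(0.16/n). On the pooled rate n = 21 under 2:1 and under 1:1, so it is 0.087 either way. On the exercise arm alone, 2:1 gives √(0.16/14) = 0.107, against √(0.16/10.5) = 0.123 for an average 1:1 arm. The gain exists only for a rate that Table 1 does not grade.

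**7. Would a rule that the worse arm sets the colour work?** Suppose true retention is the same in both arms.

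- At 85%, pooled P(≥ 17/21) = 0.80. Both arms green: P(≥ 12/14) × P(≥ 6/7) = 0.648 × 0.717 = 0.46.
- At 90%, 0.95 pooled, against 0.842 × 0.850 = 0.72.

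**The case against.** **Pooling is inferred.** The article never uses the word, and the Discussion's remark on precision makes most sense if the authors also look at the exercise arm separately. That is fair. But the definition, the single table row and the N = 21 interval all point the same way, no per-arm threshold appears anywhere, and the authors did restrict acceptability to one arm when they meant to. Tabulating by arm may be left to an analysis plan. The graded definition is not left open, because the article fixes it.

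**The colour does not decide alone.** The assessment is holistic and rests with a steering committee. Attendance and acceptability, both fundamental, concern the exercise programme. This stands and lowers the consequence, chiefly for the exercise arm. It does not supply a retention threshold for controls.

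**Stronger readings that the document does not support**

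- A reader might infer that a failing exercise programme can pass. If failing means red, it cannot at 14/7; the worst case is amber.
- A reader might take the aerobic-training trial in the Background, where 9 of 33 in the intervention group discontinued and which is described with "Aerobic training was found to be safe, however not feasible", as a retention benchmark of 24/33 = 73%. Those were discontinuations among patients on chemotherapy, not shown to be failures to complete a final assessment. The Background also reports lower dropout on endocrine therapy, and 73% is amber on this protocol's scale.
- A reader might say that no criterion touches the control arm. Controls do enter the pooled retention rate, adherence to other study procedures is not restricted to one arm, and controls have their own evaluation questionnaire. What is missing is a control-specific retention threshold.

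**Conclusion.** The point holds in a limited form. As written, a fundamental criterion can be green at 17/21 (81%) with control retention of 3/7 (43%, red) or exercise-arm retention of 10/14 (71%, amber). The control-arm case is the more serious, because the arm's stated purpose then goes ungraded on drop-out. Separately, the Discussion's precision claim is inconsistent with a retention rate whose denominator is 21 under any allocation.

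This rests on the pooled reading and on the planned 14/7 split. The probabilities in the working depend on assumed retention rates and show only that such outcomes are not remote when the arms differ widely. The stated 62–98% interval is not in error. Because retention by arm can be recovered from data already being collected, this is a matter of definition and grading, with no loss of information.

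**What to change.** 1. In the feasibility outcomes and Table 1, report and grade retention in each arm with the existing thresholds, beside the pooled rate.
2. State that the steering committee will consider any arm that is red even when the pooled rate is green.
3. In the Discussion, limit the 2:1 precision claim for retention to exercise-arm retention.
4. Do not let the worse arm set the colour automatically. With seven controls, two losses already give amber, and at a true 85% in both arms the chance of green would fall from 0.80 to 0.46.

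**Cost.** Wording and added lines in one table; no new data. Per-arm estimates will be imprecise: exact (Clopper–Pearson) 95% intervals are about 10–82% for 3/7 and 42–92% for 10/14. Some red flags will be chance. At a true 85% in both arms, P(control ≤ 4/7) = 0.074 and P(exercise ≤ 9/14) = 0.047, so at least one arm is red with probability 1 − 0.926 × 0.953 = 0.12. That is tolerable for a flag that prompts discussion and does not override the pooled colour. With 19 of 21 participants already included at the time of writing, the change should be fixed before retention is graded.

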### Effect outcomes

Multiple effect outcomes will be explored as described below.

#### Metabolic health

Metabolic health is estimated by calculating a metabolic score. The metabolic score consists of mid-level blood pressure [(systolic blood pressure + diastolic blood pressure)/2], glucose, and triglycerides. The score will be calculated as the sum of Z-transformed levels, with glucose and triglycerides log-transformed. This method of using metabolic score is also applied in Sun et al. [54] and Dieli-Conwright et al. [36]. Blood pressure is measured with an automated blood pressure cuff with the subjects seated quietly for at least 5 min before measuring three times, with 2 min between each measurement [55]. The average of the last two blood pressure recordings is used if the difference in systolic blood pressure is less than 5 mmHg.

#### Body composition

Bioelectrical impedance analysis is measured with the TANITA MC-780MA-N multifrequency segmental body composition monitor to assess changes in weight, BMI, fat mass, muscle mass, visceral fat, basal metabolic rate, and total body water [56].Waist and hip circumference are measured according to the World Health Organization (WHO) [57], measuring waist circumference at the midpoint between the lower margin of the last palpable rib and the iliac crest and hip circumference around the widest portion of the buttocks. A waist-hip ratio is calculated.

#### Obesity-related biomarkers

Fasting blood samples (> 4 h of fasting) are assessed for levels of the following biomarkers: high-density lipoprotein, low-density lipoprotein, triglycerides, total cholesterol, plasma glucose, HbA1c, thyroid stimulating hormone, free T4, total T3, C-reactive protein, total leucocytes, differential count of leukocytes, albumin, alanine aminotransferase, hemoglobin, and thrombocytes.

#### Physical performance

Hand grip strength (HGS) is measured with a Saehan DHD-1 digital hand dynamometer. HGS is correlated with all-cause mortality, overall functional status, and physical performance in patients with advanced cancer [58]. In this study, HGS is measured in both hands at least three times while the participant is in a seated position with the arm concerned laying on an armrest and the wrist in a neutral position [59].Maximal oxygen uptake (VO^2^_max_) and fitness rating are assessed with a Watt-max test on a cycle ergometer [60] performed by an experienced physiotherapist or trained personnel.Sit-to-stand in 30 s is measured following a test manual from the Danish Association of Physiotherapists [61]. It is a validated measure of physical performance and lower limb power [62, 63].

